**Figure 3 figure3:**
[figure not shown]
Summary of the 12-week home exercise program for the follow-up group.

### Measurement

#### Feasibility

In determining the feasibility of the telemedicine approaches for the delivery of an exercise intervention, recruitment, adherence, and completion rates will be measured. Recruitment rate will be calculated by dividing the study sample by the total number of contacted potential participants [19]. Adherence rate is defined as the percentage of the exercise intervention sessions completed per participant [20]. To monitor participants’ adherence to the exercise intervention, data exported from the activity monitor (Polar watch) will be recorded by study personnel on an activity log for all participants in both groups. Finally, completion rate is defined as the number of participants that completed the exercise intervention as a percentage of the overall number of participants that began the intervention [20].

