### Statistical Analysis

As this is a feasibility study, the testing procedure will be assessed rather than only focusing on the potential outcomes of the intervention. To determine the optimal clinical practice of telemedicine for an exercise intervention, recruitment, adherence, and completion rates of 2 randomized groups (supervised and follow-up approaches) will be investigated. Descriptive statistics will be presented as means and SDs. Based on previous research on home-based exercise interventions [23], the adherence rate will be assessed with a set threshold of 80%. A Wilcoxon rank sum test will be used to evaluate the adherence rate and compare both telemedicine approaches. Whereas both recruitment and completion rates will be compared using descriptive statistics and assessed with a set threshold of 50%. To measure the change in outcome parameters of participants’ muscle strength and cardiopulmonary fitness, pre- and postintervention evaluation results will be assessed with a Friedman ANOVA. A Kruskal-Wallis test will be used to determine the differences in outcome parameter changes between the 2 groups (supervised and follow-up groups).

To assess the cost-effectiveness of the 2 telemedicine approaches, a cost-effectiveness plane and an incremental cost-effectiveness ratio will be computed. The incremental cost and incremental effect will be plotted on a cost-effectiveness plane, where the horizontal axis will represent the incremental cost and the vertical axis will represent the incremental effect [24,25]. The costs and clinical outcomes for both telemedicine groups will be plotted on the plane, which will visually demonstrate the additional cost per unit of health gain for each telemedicine approach. To calculate the incremental cost-effectiveness ratio, the difference in costs will be divided by the difference in mean performance outcomes between the supervised and follow-up groups.

Finally, as OI is classified as a rare disorder [1], analyses will be carried out with a significance level (α) of 0.10 [26]. Statistical analyses will be conducted using the statistical analysis software SPSS, version 25 (SPSS Inc).

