### Limitations

The limitations of this study are the technical difficulties associated with telemedicine that may arise for both study personnel and participants, such as a poor internet connection, which may lead to low-quality, incomplete, or missed training sessions for those in the supervised group. For the follow-up group, a limitation to consider is the potential that participants will not wear the heart rate monitor during the sessions, as there will not be any direct supervision to provide reminders. This would lead to missed training data, limiting the quantity of data available for comparison between the 2 groups. Although this study was designed primarily to assess the feasibility of delivering a home-based exercise intervention through telemedicine, the data collected regarding the potential change in muscle function and cardiopulmonary fitness and the small sample size of only 12 participants may limit the ability to draw any strong conclusions. As well, given the narrow age range, the results of this study are not a predictor of younger or older patient populations; therefore, a larger-scale study would be beneficial. However, given the paucity of data regarding the physiological response to exercise in youth with OI, preliminary data will provide the basis for a larger intervention study. Additionally, as OI is primarily characterized by bone fragility, given this study’s remote delivery methods, it is not possible to assess the skeletal response to the 12-week exercise program. Thus, to build upon this study and given the skeletal deficits associated with OI, future research should investigate the impact of an exercise program on bone mineral content in individuals with OI. Recent research from Sinkam et al [30] demonstrated reduced mechanical tendon properties in a dominant severe OI mouse model. Given these results and the fact that tendons are typically rich in collagen type I, in addition to investigating skeletal parameters, researchers should evaluate the physiological response of tendons in OI from an exercise intervention.

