The completion of a 12-week exercise program may present a challenge for some participants, especially during the final 4 weeks of the exercise intervention when the number of sessions increases to 3 times per week. To mitigate this potential concern, study participants in the supervised group will have the flexibility of completing missed training sessions on their own schedule and therefore have access to the exercise plan with detailed instructions, images, and videos of each exercise. Whereas participants in the follow-up group are given the flexibility of completing the training sessions when convenient to the individual rather than a rigid weekly schedule.

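### Adherence has one named source, the Polar watch export, so watch non-wear that the article links to the follow-up arm puts the comparison at risk of bias towards supervision

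*Protocol article*

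**What the plan says.** Under Measurement, Feasibility, the article gives the definition: "Adherence rate is defined as the percentage of the exercise intervention sessions completed per participant". The same paragraph names how it is monitored: "data exported from the activity monitor (Polar watch) will be recorded by study personnel on an activity log for all participants in both groups". No second source for adherence is named.

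Under Limitations, the article raises the possibility that follow-up "participants will not wear the heart rate monitor during the sessions, as there will not be any direct supervision to provide reminders". It then states the consequence: "This would lead to missed training data, limiting the quantity of data available for comparison between the 2 groups". It gives no back-up source, no rule for a session without an export, and no direction of error.

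Under Statistical Analysis, adherence is held against an 80% threshold and tested between arms: "A Wilcoxon rank sum test will be used to evaluate the adherence rate and compare both telemedicine approaches". The significance level is 0.10. Recruitment and completion are compared descriptively, against 50%. Adherence is thus the only feasibility outcome with a between-group test.

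On sessions outside the live schedule, Limitations says: "study participants in the supervised group will have the flexibility of completing missed training sessions on their own schedule". Follow-up participants may train whenever it suits them. The article does not say whether a make-up session counts as completed in the supervised arm.

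**The concern.** The definition concerns sessions completed, but the named instrument shows only sessions during which the watch was worn and exported. The two agree only if wear is complete, and the article itself gives a reason why wear may be poorer in one arm.

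Limitations treats this as a loss of quantity. Losing data at random would cost precision. Here the loss falls on the numerator of the outcome, it is tied to the allocated arm, and it lowers the recorded value. That is potential differential misclassification, and it points the same way as the hypothesis in the Introduction and Discussion, that supervised participants adhere better.

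Two results are exposed: the Wilcoxon comparison and the follow-up arm's standing against 80%. Feasibility is the first aim, and the article intends its results to inform which approach clinicians use. An apparent advantage for supervision could be an advantage in reminding participants to wear a watch.

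**Working it through.** The article states no figure for this point (no power calculation for adherence and no non-wear rate), so there is nothing to reproduce. The calculation shows how much non-wear would matter.

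**Inputs from the article.** 6 participants per arm; alpha 0.10; threshold 80%; two sessions a week at the start and three in the final 4 weeks.

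**Assumptions.**
- Month 2 stays at two sessions a week: 8 × 2 + 4 × 3 = 28 sessions. If month 2 has three a week: 4 × 2 + 8 × 3 = 32.
- True adherence is equal in both arms: 85%, with 80% and 89% as alternatives. The 89% is the figure the Introduction cites for a supervised programme.
- Participants vary by a beta distribution with concentration 15, so at 85% the SD is √(0.85 × 0.15 / 16) = 0.089.
- The watch is always worn in the supervised arm.
- A session without an export is scored as not completed.
- The test is two-sided, and the 80% threshold applies to the arm mean; the article specifies neither.

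**Step 1: recorded adherence.** Recorded = true × share of sessions with the watch worn. At 85% true adherence: 0.85 × 0.95 = 0.8075; 0.85 × 0.90 = 0.765; 0.85 × 0.80 = 0.680; 0.85 × 0.70 = 0.595.

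**Step 2: non-wear that takes the expected mean below 80%.** 1 − 0.80/true. At 85%: 1 − 0.80/0.85 = 5.9%. At 89%: 1 − 0.80/0.89 = 10.1%.

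**Step 3: chance of a significant result when the arms truly do not differ.** Exact permutation Wilcoxon test, 4,000 simulated trials per setting (simulation standard error at most √(0.25/4000) = 0.008), 28 sessions, true adherence 85%:

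| Non-wear, follow-up only | Expected recorded follow-up adherence | Significant at 0.10 | Significant and favouring supervision | Follow-up mean at least 80% |
|---|---|---|---|---|
| 0% | 85.0% | 0.09 | 0.05 | 0.86 |
| 5% | 80.75% | 0.16 | 0.15 | 0.59 |
| 10% | 76.5% | 0.34 | 0.34 | 0.22 |
| 20% | 68.0% | 0.75 | 0.75 | 0.002 |
| 30% | 59.5% | 0.96 | 0.96 | 0.00 |

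The supervised mean reached 80% in about 0.86 of trials in every row. The first row is near 0.09 rather than 0.10 because the largest attainable exact level for 6 against 6 without ties is 0.093.

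**Step 4: sensitivity.** Across true adherence of 80% to 89%, the chance of a significant result is 0.13 to 0.19 at 5% non-wear, 0.27 to 0.44 at 10%, and 0.64 to 0.85 at 20%. With 32 sessions the ranges are 0.14 to 0.21, 0.27 to 0.46 and 0.65 to 0.87. With full capture in both arms it is 0.084 to 0.094 throughout.

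**Step 5: can the missing-data reading avoid this?** If each session without an export were removed as missing, only sessions with an export would remain, and every participant with any export would score 100%. With the watch as the only source, the choice is between scoring unexported sessions as missed and having no usable adherence rate.

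**The case against.** The strongest reply is that the article never says an unexported session is scored as missed. It defines adherence by completion, and its wording on non-wear suggests missing data. The coding rule could sit in the full protocol or analysis plan. The kinesiologist also meets each follow-up participant every 4 weeks to review progress, so unrecorded sessions could come to light. This is a 12-person pilot that discloses the limitation.

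Part of that stands: the coding rule is an assumption here, and every figure above depends on it. But no coding rule can separate two events that leave the same record, and the article does not say that the 4-weekly meetings feed the adherence figure. It has chosen the instrument, named its arm-specific weakness and described the effect as lost quantity only.

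Several stronger readings are tempting, and the document does not support them:

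- **That the plan expects follow-up participants to forget the watch.** It speaks of a potential.
- **That the watch is declared the only source.** This is inferred from no other being named.
- **That the comparison is biased.** No non-wear rate is given, and supervised wear is not said to be complete. Supervised make-up sessions are done alone and face the same risk. With wear shares for each arm, the expected spurious difference is true adherence × (supervised share − follow-up share), so any non-wear in the supervised arm shrinks it.
- **That make-up sessions also favour supervision.** If 25% or 50% of missed supervised sessions were made up and counted, with no equivalent in follow-up and no non-wear, the rejection rate would be 0.13 or 0.33. That premise is not in the article, which gives follow-up participants open scheduling too. A make-up session that was done is a completed session under the article's definition. What remains is that the text does not say whether it counts, so the supervised figure may mix live and solo sessions.
- **That the supervised arm should be held to 80% on live-attended sessions alone.** This would apply unequal rules. If both arms completed 85%, with 70% live and 15% made up in the supervised arm, they would score 70% and 85%.

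**Conclusion.** The concern holds as a risk of bias. The one named source cannot distinguish an unworn-watch session from a missed one in the unsupervised arm. The article links non-wear to that arm, and the resulting error would favour the hypothesised result. Describing this as a reduced quantity of data understates it.

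Modest non-wear would be enough. On the assumptions listed, 10% in follow-up only raises the chance of a spurious difference from about 0.09 to about 0.34 (0.27 to 0.44 across true adherence of 80% to 89%), and about 6% takes the expected follow-up mean below 80% when true adherence is 85%. These figures illustrate sensitivity; they do not estimate what will happen. They rest on equal true adherence, full wear in the supervised arm, the assumed spread and session count, and unexported sessions being scored as missed. The remedy has to be in place before data collection, because sessions that nobody logged cannot be recovered later.

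**What to change.** 1. Add a short participant or parent session log in both arms, checked at the same 4-week points. Follow-up participants already have a meeting then; the supervised arm needs the same check.
2. Count a session as completed, in either arm, if the watch or the log shows it.
3. Report watch-only adherence as the lower bound and watch-or-log adherence as the upper bound. Apply the 80% criterion and the Wilcoxon test to both. If the two disagree, say that the comparison depends on how sessions were captured.
4. In the supervised arm, report live-attended and make-up sessions separately as description only. Apply the same completed-session rule and the same 80% criterion to both arms.
5. Reword the Limitations paragraph so that non-wear is described as a potential bias towards the supervised arm as well as a loss of data.

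The cost is a one-line entry per session, a brief check every 4 weeks and a few extra rows in the results. The drawback is that self-report can overstate adherence, which is why both bounds are shown.

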#### Cost

To determine the cost comparison between the 2 groups, the number of hours spent by the kinesiologist delivering the exercise intervention to the supervised group will be recorded and compared to the number of hours spent with participants in the follow-up group. The kinesiologist will be paid a rate which is commensurate with their previous experience as well as a wage that aligns with the rate of pay for a kinesiologist in the market in which this study is conducted. The equipment costs (Microsoft Teams, Polar heart rate monitor, resistance band, and weighted exercise ball) will be reported and included in the calculations. When drawing cost comparisons for the 2 approaches, the supervised approach is a group approach, whereas the follow-up approach is an individualized approach. Therefore, a direct comparison between the 2 approaches presents a challenge. Nevertheless, to mitigate the difference in group and individualized approaches, the cost comparison for both the supervised and follow-up groups will be computed and presented as a cost per participant.

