Telemedicine is a method for the remote delivery of professional health services at a distance by linking clinicians and patients through information technology [10,11]. Lambert et al [12] used a telemedicine approach for the delivery of a 16-week home exercise program for pediatric acute lymphoblastic leukemia survivors. This supervised telemedicine approach was shown to be feasible, as the results demonstrated a mean adherence rate of 89% and a completion rate of 75% [12]. In contrast, Gagnon et al [13] used a follow-up telemedicine approach for the delivery of a 12-week home exercise program for youth with arthrogryposis multiplex congenita, where clinicians conducted follow-ups with study participants every 3 weeks. The results showed a 68% adherence rate and a 64% completion rate, which was sufficient for most study participants to achieve their goals [13]. As the recent literature demonstrates, the follow-up approach may be less effective as it led to a lower completion rate [12,13]. However, additional clinician time cost associated with the supervised approach may exceed the increase in benefits associated with constant supervision.

There remains a gap in the literature with respect to the comparison between supervised and follow-up telemedicine approaches and the associated cost-effectiveness of both approaches. Hence, the aim of this study is to evaluate the feasibility and cost-effectiveness of 2 telemedicine approaches (supervised vs follow-up) for the delivery of a home exercise program. The secondary aim of the study is to investigate the effectiveness of the home-based exercise program on muscle function and cardiopulmonary fitness in youth with OI type I. Given the aims of this study, it is hypothesized that participants in the supervised group will have higher adherence and completion rates compared to the follow-up group, which will be further associated with greater increases in muscle strength and cardiopulmonary fitness from the exercise intervention. However, the additional intervention delivery time required for the supervised group may make it less cost-effective compared to the follow-up approach.

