#### Exercise Intervention

The exercise intervention will begin with 35 minutes twice a week, including a warmup and cooldown, each 5 minutes in duration. Every 4 weeks, the training will intensify in either duration of exercise or number of sessions per week, which is required to stimulate physiological adaptation and enhance improvement [7]. For the duration of the intervention, a kinesiologist (human movement specialist) will provide training and supervision to participants in the supervised group at home through live video sessions. Participants in the supervised group will be separated into 2 groups of 3 participants. For the follow-up group, the kinesiologist will meet with participants individually every 4 weeks to review their progress, preview the next month’s exercise plan, and address any concerns or challenges the participants may have. The exercise program timelines for both groups are outlined below (Figures 2 and 3).

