#### Cost-Effectiveness

To compare the cost-effectiveness of the 2 telemedicine approaches, a bottom-up approach will be used, a method for the assessment of each resource required to provide health care and assigning the related costs accordingly [21,22]. For both the supervised and follow-up groups, the mean performance outcome for each of the 5 preintervention evaluation tests will be computed. These means are then compared within their group (supervised or follow-up) to a mean for the same 5 postintervention evaluations, determining the mean outcome (increase or decrease) for each of the 5 tests. These mean outcomes will then be compared to the total cost of each telemedicine approach to determine the cost (on a per-unit basis) of the health outcome. Doing so allows for the assessment of not only which telemedicine approach has a higher cost overall, but most importantly, the per-unit cost of the health outcome for the supervised and follow-up groups. This provides a more accurate comparison, with respect to financial costs, of the 2 methods.

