**Kinesiologist**
Evaluations2 hours (preintervention evaluation)+2 hours (postintervention evaluation)×6 participants=24 hoursInterventionEstimated time required for the supervised approach
(8 hours [month 1]+12 hours [month 2]+18 hours [month 3])×2 (number of groups)=76 hours
24 hours (evaluations)+76 hours (intervention)=100 hours
Total: 100 hours (total hours)×CAD $27 (US $20) (hourly rate)=CAD $2700 (US $2006)
Estimated time required for the follow-up approach
(2 hours [month 1]+2 hours [month 2]+2 hours [month 3])×6 (number of participants)=36 hours
24 hours (evaluations)+36 hours (intervention)=60 hours
Total: 60 hours (total hours)×CAD $27 (US $20) (hourly rate)=CAD $1620 (US $1204)

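### The ICER sets the recorded cost of a whole arm against group means that can omit participants who stop, the hours saved by stopping differ by arm, and the cost denominator is left open

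*Protocol article*

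**What the plan says.** All references are to the protocol article.

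- **Cost.** Clinician cost rests on hours actually spent: "the number of hours spent by the kinesiologist delivering the exercise intervention to the supervised group will be recorded", and these are compared with the hours spent on the follow-up group. Equipment is added. The section accepts that group and individual delivery are hard to compare and answers this by expressing cost per participant. It does not say whether that means randomised, started or completed.
- **Cost-Effectiveness.** A pre mean and a post mean are formed for each test in each arm. Then: "These mean outcomes will then be compared to the total cost of each telemedicine approach".
- **Statistical Analysis.** The incremental cost-effectiveness ratio (ICER) is the between-arm difference in costs over the between-arm difference in mean performance outcomes.
- **Exercise Intervention.** The delivery unit differs by arm. Supervised: "Participants in the supervised group will be separated into 2 groups of 3 participants". Follow-up: "the kinesiologist will meet with participants individually every 4 weeks".
- **Textbox 1.** The hours scale accordingly. Supervised: "8 hours [month 1]+12 hours [month 2]+18 hours [month 3])×2 (number of groups)=76 hours". Follow-up: "2 hours [month 1]+2 hours [month 2]+2 hours [month 3])×6 (number of participants)=36 hours". Each arm also carries 24 evaluation hours.
- **Introduction and Discussion.** Lower completion is expected under follow-up. The cited supervised programme had 75% completion. For the cited follow-up programme, "The results showed a 68% adherence rate and a 64% completion rate".

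**The concern.** Cost-effectiveness is part of the main objective, and the question is whether the extra clinician time is worth its price. That needs cost and effect to describe the same people. As the sections are worded, cost covers everyone who used resources, while a participant without a post evaluation contributes nothing to the post mean. The hours not delivered to that participant are saved, but the benefit that participant did not obtain is not counted.

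The saving is also uneven. A follow-up stop removes that person's remaining meetings. A supervised stop removes no session hours while anyone in the same group of three continues. If follow-up loses more people, as the protocol expects, the cost side of the ICER can move against supervision partly because supervision kept people in.

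Dividing by participants does not settle this, because the direction of the shift depends on which participants are counted.

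**Working it through.** **Inputs (Textbox 1 and Table 2).** Rate CAD 27 per hour. Evaluations 2 h pre and 2 h post per participant. Supervised sessions 8, 12 and 18 h per group in months 1 to 3, two groups. Follow-up meetings 2 h per participant per month. Equipment 1646 and Microsoft Teams 74 per arm (1720 together), treated as fixed.

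**Reproducing the plan.**
- Supervised: 24 + 38 × 2 = 100 h. The textbox has "100 hours (total hours)×CAD $27 (US $20) (hourly rate)=CAD $2700 (US $2006". 2700 + 1720 = 4420; ÷ 6 = 736.7.
- Follow-up: 24 + 6 × 6 = 60 h; × 27 = 1620; + 1720 = 3340; ÷ 6 = 556.7.
- Increment: 4420 − 3340 = 1080, or 180 per participant. Table 2 agrees (its 736 and 556 are sums of rounded components).

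**Saving per stop.** Assumptions: remaining individual meetings and the post evaluation are not held, and supervised sessions continue for the rest of the group.

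| Stop after month | Follow-up saves | Supervised saves | Ratio |
|---|---|---|---|
| 0 | 6 + 2 = 8 h, CAD 216 | 2 h, CAD 54 | 4 |
| 1 | 4 + 2 = 6 h, CAD 162 | 2 h, CAD 54 | 3 |
| 2 | 2 + 2 = 4 h, CAD 108 | 2 h, CAD 54 | 2 |

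If the post evaluation is still held, the savings are 6, 4 or 2 h in follow-up and none in supervised.

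**Effect on the increment, all stops after month 1 (CAD).**

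| Stops, follow-up / supervised | Follow-up cost | Supervised cost | Increment | Gap per randomised | Gap per completer |
|---|---|---|---|---|---|
| 0 / 0 | 3340 | 4420 | 1080 | 180 | 180 |
| 1 / 0 | 3178 | 4420 | 1242 (+15%) | 207 | 4420/6 − 3178/5 = 101 |
| 2 / 1 | 3016 | 4366 | 1350 (+25%) | 225 | 4366/5 − 3016/4 = 119 |
| 3 / 0 | 2854 | 4420 | 1566 (+45%) | 261 | 4420/6 − 2854/3 = −215 |

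Three of six completing is 50%, the completion threshold given under Statistical Analysis, so the last row is not outside what the plan would accept as feasible.

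**At the cited completion rates.** Expected stops are 6 × 0.36 = 2.16 in follow-up and 6 × 0.25 = 1.5 in supervised. After month 1: 1080 + 2.16 × 162 − 1.5 × 54 = 1349 (+25%). After month 0 it is 1466 (+36%), and after month 2 it is 1232 (+14%).

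**Where the pattern does not hold.**
- Supervised loses two and follow-up one, after month 1: savings 108 against 162, increment 1134. The arm that loses fewer people saves more.
- A whole supervised group stops after month 1: 12 + 18 + 3 × 2 = 36 h (CAD 972) saved, against 3 × 6 = 18 h (CAD 486) for three follow-up stops.

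**Effect side.** Suppose completers in both arms improve by the same amount d. With two follow-up stops and one supervised stop, the completers' mean changes differ by 0. If participants who stopped are counted as unchanged, they differ by (5/6)d − (4/6)d = d/6. A completers-only effect misses that difference, while the total cost records the hours saved.

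**The case against.** The strongest objection is that hours not delivered are resources not used, and bottom-up costing is meant to capture exactly that. This stands: recording actual hours is not an error, and dividing them by the number randomised is legitimate.

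Second, the article does not say that participants who stop miss the post evaluation or that the effect uses completers only, and handling of missing tests may sit in a document not shown. This also stands in part. The missed evaluation is an assumption here. But the article does fix the form of the ratio, total arm cost against a difference of group means, and that form admits the mismatch.

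Third, the cited 75% and 64% come from other populations and programmes, and not completing the exercise does not prove that the monthly meetings lapsed. Those figures only illustrate size.

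Fourth, scheduled costs are published and completion is reported by arm, so a reader could derive cost per completer. That is true, but it does not say which figure enters the ICER.

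A reader might infer that the ICER favours whichever arm loses more people, or that every follow-up stop makes that arm look cheaper. The documents support neither. The two exceptions in the working contradict the first. The second is true only for total or per-randomised cost; per completer, a single follow-up stop raises that arm's cost from 557 to 636. Use of total cost in the Cost-Effectiveness section and division by six in Table 2 point towards the total or per-randomised reading, but the article does not fix it.

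**Conclusion.** The concern holds in a limited form. The defect is that cost and effect can describe different people and that the denominator is open; it is not the recording of hours.

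On total or per-randomised cost, a follow-up stop lowers recorded cost 2 to 4 times as much as a supervised stop, unless a whole supervised group stops. One or two stops in an arm of six are enough to matter: two follow-up stops and one supervised stop move the increment by CAD 270 (1350 − 1080). For a given difference in effect, the ICER rises by the same 25%. With three follow-up stops and none in supervised, the cost side changes sign with the denominator.

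These sizes rest on the published hours, on assumed times of stopping, and on a missed post evaluation. If the evaluation is held, the population mismatch largely goes, and what remains is a real saving that can be set against that person's own outcome.

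**What to change.** In Cost, Cost-Effectiveness and Statistical Analysis:

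1. Use all randomised participants on both sides of the ICER: recorded cost divided by the number randomised, and mean within-person change in place of a difference between separately formed pre and post means.
2. Invite participants who stop to the remote post evaluation at the scheduled time.
3. For those still without a post test, add a sensitivity analysis that assumes no change.
4. Report as sensitivity results the ICER at the scheduled hours of Textbox 1, which shows how much of the cost gap comes from stopping, and the cost per completer by arm.

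The cost is small. The post evaluation of all six participants is already inside the 24 evaluation hours budgeted per arm, and the rest is wording and a few extra ratios from data already collected. The downside is a little more analysis, and the follow-up approach may look less favourable than its recorded total suggests.
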